**Trial registration number::**

ChiCTR2000033274

## Introduction

1

Feeding disorders fall into 3 categories under the Chatoor criteria:^[1]^

(1)feeding disorders of state regulation;(2)feeding disorders of reciprocity; and(3)pediatric anorexia (PN).

PN refers to children with a sustained loss of appetite, who eat less and/or dislike eating. As a disorder of chronic hunger, PN is common in children, with a prevalence of 5% to 10%.^[2]^ The disease is most common in children aged 1 to 5 years.^[3]^ If left untreated, PN can result in childhood malnutrition, body wasting, rickets, anemia, and a decline in immune function, all adverse consequences that can affect growth and development both physically and intellectually, in addition to mental illness.^[4–5]^ In modern medicine, the main treatment for PN is drug treatment, including the use of supplementary trace elements to enhance peptin levels and gastric dynamics^[6]^ However, it is often difficult to determine the exact cause of anorexia in children.^[7]^ Due to the poor compliance of children on oral drugs and the high occurrence of side effects,^[8]^ their clinical application is limited.

As a painless and non-drug therapy, infantile massage is widely applicable to the pediatric disease spectrum, with the advantages of simple operation and a comfortable experience. In clinical practice, massage represents a dominant therapy for PN. Through many years of clinical practice, it has been shown that children with anorexia who receive massage therapy not only significantly improve their appetite, but relieve sallow complexion, abdominal distension, and other accompanying symptoms. Modern medical studies have shown that massage therapy can increase vagus nerve activity and promote appetite regulatory factors, thus increasing gastrointestinal peristalsis^[9]^ and improving digestive function. Massage intervention also correlates with improves the correlation between the brain and intestine axis, intestinal flora activity, and the regulation of host metabolism.

In this study, we explore the biological mechanism(s) of anorexia from the perspective of intestinal flora and the regulation of host metabolism. We further reveal the action site and therapeutic mechanism(s) of pediatric massage for the treatment of anorexia. This furthers our understanding of the optimal treatment methods for the treatment of PN in the clinic.

## Methods

2

### Study design

2.1

This single-blind, randomized controlled clinical study will follow the ethical principles of the Ministry of China's Ministry of Health “Ethical Review Measures for Biomedical Research Involving Human Beings (2007)”, the SFDA “Standard for Quality Management of Drug Clinical Trials (2003)”, “The Regulations on Clinical Trials of Medical Devices (2004)”, the WMA “Helsinki Declaration”, the CIOMS “International Ethical Guidelines for Biomedical Research on Human Beings”. The project was evaluated and approved by the Research Ethics Committee of Gansu Provincial Hospital of Traditional Chinese Medicine. (Ethical batch No. FJ/04-IRB/C/018-V3.0, Ethics Review Adoption Form places in the Supplemental Digital Content) Treatments are to be performed in the Gansu Provincial Hospital of Traditional Chinese Medicine from January 1, 2020 solstice and December 31, 2023. Arrangements for pre-intervention, intervention, and evaluation are shown in Supplementary Material 1. The flow chart of each stage of the study are shown in Supplementary Material 2.

### Research subjects

2.2

All children meeting the eligibility criteria will be recruited through the Department of Pediatrics and Acupuncture and Massage at the Gansu Hospital of Traditional Chinese Medicine. At the time of admission, members of the research group will explain all relevant study content to the subjects and their families. Signed informed consent forms will be provided by all participants.

### Inclusion criteria

2.3

All subjects will be required to meet the known diagnostic criteria for anorexia in children.^[1]^ The criteria include

(1)a refusal to eat adequate amounts of food for at least 1 month;(2)a failure to communicate hunger and a lack of interest in food;(3)significant growth deficiency;(4)a refusal to eat that is unrelated to an underlying medical illness or a traumatic event;(5)aged 2 to 12;(6)agree to receive massage therapy;(7)consent to the study either directly or through a legal guardian.

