#### Blank group

2.7.2

No interventions will be performed.

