### Randomized grouping

2.8

A total of 60 healthy children will be randomly selected for physical examinations. A statistical expert not involved in the design of the study will use SPSS 22.0 software to generate a series of random sequences, which will be marked onto a card and placed in a sealed envelope. Each subject will receive an envelope at a time-point consistent with the test conditions. Subjects will be randomly divided based on their number into control or test groups (n = 60 per group). For each child, the chiropractor will open the envelope to obtain the grouping code.

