##### Structure of the intestinal flora

2.11.1.1

Feces samples from 3 groups of children will be collected and stored at −80 °C. Total genomic DNA will be extracted from all feces samples using commercial DNA purification kits as per the manufacturer's recommendations. Samples will be stored at −20 °C after qualitative detection. Concentrations will be determined through 0.8% agar-gel electrophoresis. For the detection of the 16S rRNA V6 region, the upstream primer 967F (CNACGCGAAGAACCTTANC) and downstream primer 1046R (CGACAGCCATGCANCACCT) will be used for all amplification reactions. The amplification system was 25uL, Takara Ex Taq was used, and the template was 2 uL. Amplification conditions will be as follows: 94 °C for 2 minutes; 94 °C for 30 seconds; 57 °C for 30 seconds; 72 °C for 30 seconds (× 30 cycles); final extension of 72 °C for 5 minutes.

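### The inclusion criteria cannot apply to the 60 healthy children, and no separate age range, exclusions or matching is stated for this non-randomised group, so its contrasts with patients may be confounded by age

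*Protocol article*

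**What the plan says.** Section 2.3 (Inclusion criteria) opens with "All subjects will be required to meet the known diagnostic criteria for anorexia in children". The list that follows includes "3)significant growth deficiency" and "5)aged 2 to 12;(6)agree to receive massage therapy".

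Section 2.8 (Randomized grouping) brings in a different population: "A total of 60 healthy children will be randomly selected for physical examinations". Randomisation is then limited to two groups: "Subjects will be randomly divided based on their number into control or test groups (n = 60 per group". Section 2.7.2 says of the blank group that "No interventions will be performed". The article never says outright that the healthy children are the blank group, but no other reading fits three groups of 60.

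The healthy children take part in the main comparison. Section 2.11.1.1 says "Feces samples from 3 groups of children will be collected", and the Abstract has the groups compared on flora, SCFAs and the other measures. Section 2.11.6 (Statistical analysis) names 1-way ANOVA with pairwise follow-up tests, and rank sum tests where normality fails. It names no covariate.

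**The concern.** Taken literally, section 2.3 bars every healthy child, because each would need an anorexia diagnosis and a growth deficit. Taken as a list for patients, it leaves one third of the children (60 of 180) with no stated entry rule beyond being healthy and selected for examination.

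Randomisation balances age between massage and control. Nothing stated in the article does so between healthy children and patients. The Introduction says of the condition that "The disease is most common in children aged 1 to 5 years", so patients may well sit in the lower part of the 2 to 12 range, while the healthy children's ages are unspecified. The Discussion itself links disturbed flora in childhood to an immature gut ecosystem, so age is a plausible cause of differences in the main outcome. If the groups differ in age, a difference due to maturation could be read as a difference due to anorexia, or a real difference could be masked.

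**Working it through.** **1. The two readings of section 2.3**

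| Reading | Consequence for the healthy children |
|---|---|
| The list covers everyone | The 2 to 12 age limit applies, but so do the diagnosis and the growth deficit, so none can enter |
| The list covers patients only (the Abstract points this way) | They can enter, but with no stated age range or matching, and it is unclear whether the exclusions in 2.4 apply |
| Only the age item is carried over | They share the 2 to 12 range, but a band that wide does not balance age without matching |

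Each reading leaves something to settle.

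**2. What an age imbalance could do**

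No figure in the plan can be reproduced here. The 60 per group comes with no effect size, SD or power, and the point does not depend on one.

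Inputs:
- From the article: 60 healthy children, 60 per patient group, significance level .05.
- Assumed: a two-sided test; an outcome linearly related to age; a difference in mean age of *s* SDs of age (0.25, 0.5 or 1.0); an age-outcome correlation *r* of 0.2, 0.3 or 0.5.

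Formulas (Φ is the standard normal distribution function):
- Spurious standardised difference: b = s × r
- Standard error of a standardised difference at 60 v 60: √(2/60) = 0.183
- Rejection rate with no true disease difference: Φ(b/0.183 − 1.96) + Φ(−b/0.183 − 1.96)

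Worked case, s = 0.5 and r = 0.3: b = 0.5 × 0.3 = 0.15 SD, and b/0.183 = 0.82. The rate is Φ(−1.14) + Φ(−2.78) = 0.127 + 0.003 = 0.13.

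Spurious difference and false-positive rate over the range:

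| Age imbalance (SD) | r = 0.2 | r = 0.3 | r = 0.5 |
|---|---|---|---|
| 0 | 0; 5.0% | 0; 5.0% | 0; 5.0% |
| 0.25 | 0.05; 5.9% | 0.075; 7.0% | 0.125; 10.5% |
| 0.5 | 0.10; 8.5% | 0.15; 13.0% | 0.25; 27.8% |
| 1.0 | 0.20; 19.5% | 0.30; 37.6% | 0.50; 78.2% |

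For scale, if ages were spread evenly over 2 to 12, the SD would be 10/√12 = 2.9 years. An imbalance of 0.5 SD would then be about 1.4 years.

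**The case against.** The strongest reply is that the conflict is only one of wording. In the Abstract and in section 2.8 the healthy children are mentioned first, and the word subjects is then used for those who are randomised. The Abstract also ties the inclusion criteria to children with anorexia. On that usage section 2.3 never meant the healthy children, and nobody would screen them for anorexia. This stands as far as it goes: the contradiction is minor. But it leads straight to the reading on which the healthy group has no stated age range or matching.

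A second reply is that this is a condensed article. Its supplementary schedule and flow chart are not shown, reference-group criteria may sit in the full protocol, and covariate adjustment is often left to an analysis plan. That is fair, and it limits how firmly one can speak of an omission. It does not remove the conflict in the printed text. The article also names a method, and that method as stated sets randomly selected healthy children against patients with no age term.

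Third, the arithmetic rests on assumed inputs, and several of the resulting biases are small. A bias of 0.15 SD is well below the observed difference needed for P < .05 at 60 v 60, which is t(.975, 118) × √(2/60) = 1.98 × 0.183 = 0.36 SD. That is true, but a bias need not reach the threshold by itself. Added to sampling error it still raises the false-positive rate, as the table shows.

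A reader might infer more than the article supports:
- That the contrast *is* confounded. No ages are given for the healthy children, so this is a risk and has not been shown.
- That the healthy children have no age limit at all. The 2 to 12 item stands in a list headed as applying to every subject, so the intent may have been to cover them.
- That children attending examinations are older than the patients. Nothing in the article says so, and an imbalance either way would matter.
- That the healthy group will be used to judge whether massage returns flora to normal. The article states no such purpose.

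**Conclusion.** The point holds in a limited form. Section 2.3 as worded cannot apply to the healthy children. Read as covering patients only, it leaves this non-randomised group without a stated age range, exclusions or matching. Healthy-versus-patient contrasts in flora and SCFAs, analysed by unadjusted 1-way ANOVA, may be confounded by age in either direction.

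The actual size is unknown. Over the assumed range, the false-positive rate runs from 5.9% (0.25 SD imbalance, correlation 0.2) to 78.2% (1.0 SD, correlation 0.5), with 13% at the middle values. These figures assume a linear age effect and no true disease difference.

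The randomised massage-versus-control comparison is not affected, because randomisation balances age in expectation. The change is therefore worth making for the healthy-group contrasts, and the treatment comparison does not depend on it.

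**What to change.** 1. Reword section 2.3 so that it covers the randomised children only.
2. State that the healthy children are the blank group, and give them their own criteria: age 2 to 12, no anorexia, and those exclusions in section 2.4 that apply to them.
3. Frequency-match them to the randomised children by age band and sex. The bands 2 to 6 and 7 to 12 already appear in section 2.7.1 and could serve.
4. Replace the unadjusted 1-way ANOVA with an age-adjusted model, such as ANCOVA, for every healthy-versus-patient comparison. Matching in broad bands leaves age differences within bands, so the adjustment is still needed.

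The cost is a change of protocol wording, age-by-sex quotas and slightly slower recruitment of healthy children. No extra children are needed. Matching has to be in place while the healthy children are being enrolled; afterwards only adjustment remains.

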### Exclusion criteria

2.4

(1)Patients with heart, brain, liver, kidney, systemic diseases, or acute infection;(2)local skin breakage on the back or area of massage;(3)anorexia due to other diseases (e.g., anorexia nervosa);(4)receiving other treatments for anorexia in the past month;(5)participation in other clinical trials.

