### End of study/discontinuation

2.10

The study will be discontinued when the following complications are encountered:

(1)serious adverse events or specific physiological changes;(2)voluntarily discontinuation;(3)poor compliance, including a failure to cooperate or comply with treatment after repeated explanations by the clinician;(4)receiving food or alternative treatments for anorexia;(5)results of those exceeding half of the total course of treatment available for inclusion in the statistical analysis of treatments.

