## Limitations of the study

5

1.The control group drug will receive a widely used clinical drug that is recommended by Chinese guidelines. Its safety and efficacy have been proven through years of clinical application, but it is not currently recommended in relevant international guidelines.2.All subjects are of the same ethnicity. Whether massage therapy is effective for other ethnicities/regions requires confirmation in future multi-center and large-sample trials.3.Intestinal flora are susceptible to a variety of factors, particularly dietary factors.^[23]^ It is therefore difficult to exclude the influence of diet on the digestive tracts of the children. This study will provide dietary and water guidance, providing suggestions to minimize the bias in the final results.

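### The listed exclusions and the on-study rule restrict other treatment only when it is given for anorexia, so recent antibiotics and probiotics taken for other reasons are allowed although gut flora is a main outcome

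*Protocol article*

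**What the plan says.** Section 2.11.1.1 of the protocol article lists "Structure of the intestinal flora" under the main outcomes and states that "Feces samples from 3 groups of children will be collected". Faecal SCFAs come next (2.11.2), ahead of the secondary outcomes, and section 4 describes the faecal tests as the main indicator.

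Section 2.4 prints a numbered list of five exclusions. Two bear on this point:
- Item 1: "Patients with heart, brain, liver, kidney, systemic diseases, or acute infection".
- Item 4: "receiving other treatments for anorexia in the past month".

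During the study, the only rule on other treatment is the discontinuation criterion in section 2.10: "receiving food or alternative treatments for anorexia".

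Section 5 concedes that "Intestinal flora are susceptible to a variety of factors, particularly dietary factors". The control it offers is: "This study will provide dietary and water guidance, providing suggestions to minimize the bias in the final results".

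Antibiotics, probiotics, prebiotics and concomitant medication are not mentioned anywhere in the article.

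**The concern.** For an outcome measured on stool bacteria, what matters is whether a product acts on those bacteria, not why it was taken. Both treatment rules are written by indication. A course of antibiotics finished shortly before the baseline stool, or a probiotic taken for an unrelated reason, passes both.

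The baseline stool, the final stool or both could then reflect a drug effect unrelated to massage. Two things are at stake: the precision of the massage-versus-tablet contrast, and the interpretation of any difference from the healthy children. If exposure is not recorded at the time, it cannot be recovered reliably afterwards.

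**Working it through.** **Reading the rules against plausible exposures.** The plan states no figure on this point, so there is nothing to reproduce. The main check is what each rule reaches.

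| Exposure | Reached by a stated rule? |
|---|---|
| Child with acute infection at entry, perhaps on antibiotics | Yes, 2.4 item 1 (through the infection, not the drug) |
| Antibiotic course completed shortly before entry | No; item 1 gives no look-back and item 4 is limited to anorexia |
| Probiotic taken for poor appetite before entry | Yes, 2.4 item 4, within the past month |
| Probiotic started for poor appetite on study | Yes, 2.10 item 4 |
| Probiotic taken for another reason, before or during the study | No |
| Antibiotic given during the 4-week treatment period | No |

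**Consequence by comparison.**
- *Massage versus tablets.* Section 2.8 randomises 60 per group, so prior use is balanced in expectation. What remains is extra variance and chance imbalance. The one-way analysis of variance in 2.11.6 names no covariate for such exposure.
- *Either arm versus healthy children.* The 60 healthy children are outside the allocation, so nothing balances their use against that of the anorexia groups. If use differs, the comparison is confounded.

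**Illustrative size.** The exposure proportion p and the shift d (in SD units of a flora index) are both assumed; only n = 60 per group comes from the document. For a single measurement with within-group variance 1, a mixture of exposed and unexposed children adds variance p(1 − p)d², and the effective size is 60 / (1 + added variance).

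- p = 0.10, d = 1: 0.10 × 0.90 × 1² = 0.09, a 9% rise; 60 / 1.09 = 55.0 per arm.
- p = 0.15, d = 1.5: 0.15 × 0.85 × 1.5² = 0.287, a 29% rise; 60 / 1.287 = 46.6 per arm, a loss of about 22% (1 − 1/1.287 = 0.223).

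The abstract says groups are compared before and after treatment. If change scores are analysed, only the difference between the shifts at the two stools enters, so a pre-entry exposure that still affects the final stool partly cancels and the rise is smaller.

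**The case against.** **Condensation.** A journal article leaves detail to the full protocol, and rules on concomitant medication, case report form fields and sensitivity analyses usually sit there or in the analysis plan. This stands for those items taken alone. It does not dispose of the exclusion list, which the article prints and numbers. The authors wrote a look-back on prior treatment and tied it to anorexia, so the gap lies in a stated rule.

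**Existing criteria narrow the gap.** Acute infection is excluded, and section 2.3 requires that the refusal to eat be unrelated to an underlying medical illness. These criteria remove some children on antibiotics at entry, but not those with completed courses.

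**Bias between the randomised arms.** A reader might infer that families, who can see whether the child gets massage or tablets, would start probiotics more often in one arm and so bias the main contrast. The most plausible motive is the child's appetite, and that use already falls under 2.10 item 4. For unrelated use, the documents give no reason to expect a difference by arm.

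**The healthy group.** A reader might also infer that nothing restricts flora-altering products in the healthy children. The article gives no entry criteria for them, so what the full protocol requires cannot be known from it. The comparison is also open to other confounders whatever the antibiotic rule.

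**Size.** Every input to the variance figures except the group size is assumed, and the lower case costs little.

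**Conclusion.** The point holds in a limited form. As printed, the eligibility and on-study rules are drawn too narrowly for a flora outcome: they admit recently completed antibiotic courses and probiotics taken for reasons other than anorexia. Between massage and control the expected effect is mainly lost precision. Against the healthy group it is possible confounding, conditional on use differing.

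It would go too far to call this a major disturbance that enters uncontrolled. Section 5 supports only that flora are susceptible to several factors, and randomisation and the existing exclusions control part of the problem. The range of about 9% to 29% added variance is an illustration for a single measurement under assumed exposure and shift. It is not an estimate for this trial, and smaller inputs would give smaller values. The change is worth making because it is cheap and the exposure is hard to reconstruct later.

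**What to change.** 1. Add to section 2.4, and apply equally to the healthy group, an exclusion or deferral for systemic antibiotics, probiotics or prebiotics within a stated window before the baseline stool. The investigators should set the window and justify it for flora; the existing one-month rule was written for anorexia treatments and does not by itself supply that justification.
2. Record any such use on the case report form, in all three groups, up to the final stool.
3. Keep exposed children in the main analysis as randomised.
4. Add a sensitivity analysis that excludes samples taken after exposure. Label it supportive, because exclusion for on-study use conditions on an event after randomisation.

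The cost is one line in the eligibility list, one more case report form field, and slightly slower recruitment because some children are deferred or excluded.

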### Intervention measures

2.5

#### Massage group

2.5.1

The manipulation method will be divided into 6 stages. The child will be placed in the supine position or held by the caregiver. The following procedures will then be performed:

### Limb Massage

2.6

1.Massage will be performed using the thumb radial finger to the finger root (× 200 repetitions).2.The palm and tip of the thumb will be used to rub the horizontal grain of the proximal interphalangeal joint of the index finger, middle finger, ring finger, and little finger (× 100 repetitions).3.Kneading of the thenar will be performed with the thumb-end (× 100 repetitions).4.The PC8 (located in the center of the horizontal grain of the palm, in the middle of the second and third metacarpal bones) will be used as the center of the circle and rubbed clockwise with the thumb abdominal (× 100 repetitions).5.The ST 36 (located at the lower margin of the patella) will be pressed to 3 inches in the depression of the lateral patellar ligament by transversing the finger next to the anterior tibial ridge with low levels of force using the thumb or a threaded surface (× 150 repetitions).

